### Recruitment and randomization

Patient recruitment began in November 2008, following approval by the ethical review committees of the participating hospitals. Participating surgeons make use of an 11-item checklist to determine patient eligibility. All patients who meet the study inclusion criteria are informed by the surgeon or nurse practitioner about the study, and are given an envelope containing an information letter, a consent form and the baseline questionnaire. Eligible patients receive a phone call by a member of the research team within a few days, in order to carry out the informed consent procedures and to administer the baseline questionnaire to consenting patients. Patients are then randomized to the RGCT or the UC group in a 2:1 ratio. The computerized randomization is stratified per hospital and blocked per 9 cases [37]. These 12 random allocation sequences are generated by an independent individual, are stored in computer files, and remain unknown to the researchers until the patient is randomized. The participant as well as the treating surgeon or nurse practitioner is informed about the randomization outcome. The researchers are blinded to randomization outcome at the time of the baseline assessments, but not at the follow-up assessments. This is due to the fact that the researchers are responsible for arranging appointments with the genetic counselor for those women assigned to the RGCT arm of the study.

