### Sample size

The sample size calculations are based primarily on the type of surgery chosen, and specifically on the uptake of bilateral mastectomy. With a total sample of 255 women (170 in the RGCT arm and 85 in the UC arm), the study will have 80% power to detect a difference of 18% versus 5% in the uptake of bilateral mastectomy, with the p-value set at 0.05. The sample size ratio of 2:1 was chosen to ensure that the RGCT sample is sufficiently large to obtain stable estimates of bilateral mastectomy and delayed prophylactic contralateral mastectomy uptake among *BRCA1/2 *carriers, and to allow for secondary analyses (e.g., to examine predictors of DNA testing uptake). The percentages indicated above are based on the following assumptions: (1) based on the participating hospitals' experiences in the previous three years, 5% of the women in the UC arm are expected to choose bilateral mastectomy; (2) in the RGCT arm, it is expected that 20% will test positive for a *BRCA1 *or *BRCA2 *mutation, of whom, on average, 50% will opt for a bilateral mastectomy. Of the remaining 80% of women in the RGCT arm, we expect a 10% uptake of bilateral mastectomy. For the remaining, primarily self-report outcomes (e.g., cancer worries and cancer-specific distress, decisional satisfaction, HRQL), the sample of 255 participants is more than sufficient to detect a 0.5 standard deviation between-group difference in mean scores. Based on data obtained from the cancer registries of the Integral Cancer Centers of Amsterdam and Middle Netherlands, and on data provided by the participating hospitals, it is estimated that there will be a total of 2550 newly diagnosed breast cancer patients during the recruitment period. Approximately 15% of these women is expected to be eligible for participation. Based on prior experience with recruitment of patients into similar studies, we expect an 80% response rate. This results in an expected N of 306 patients. This allows for an attrition rate of 17%, while retaining 255 women for the primary analysis.

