### Statistical analyses

Analyses will first be performed to evaluate the comparability of the RGCT and the UC groups at study entry in terms of sociodemographic and clinical characteristics. Student's t-test or appropriate non-parametric statistics will be used, depending on the level of measurement. If the groups are not comparable on one or more background variables, those variables will be employed routinely as covariates in subsequent analyses. Between group differences in choice of surgery will be tested using the chi-square statistic or, if statistical adjustment is required for covariates, multiple logistic regression analysis. Analysis of (co)variance will be employed to assess group differences at 6 and 12 month follow-up in risk perception, psychological distress, knowledge, decisional satisfaction, and HRQL. Where appropriate, sociodemographic and clinical background variables, as well as baseline scores on the outcomes of interest, will be used as covariates. Effect sizes will be calculated using standard statistical procedures. Supplementary, descriptive analyses (both quantitative and qualitative) will be used for reporting the patients' experiences with RGCT. All primary analyses will, to as great an extent as possible, be conducted on an intention-to-treat basis. That is, all women in the RGCT group will be included in that group in the analyses, regardless of whether they actually carried through with RGCT. Supplementary analyses will be undertaken to examine sociodemographic, clinical and psychosocial factors associated significantly with (non-) attendance at the RGCT and uptake of BLM.

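### Randomisation is stratified by hospital but no stated analysis uses hospital, and baseline scores are optional covariates: a small loss on the surgery test and a possibly larger one on the scales

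*Protocol article*

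**What the plan says.** **Design.** Under Recruitment and randomization: "The computerized randomization is stratified per hospital and blocked per 9 cases". The next sentence confirms one sequence per hospital: "These 12 random allocation sequences are generated by an independent individual".

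**Surgery outcome.** Under Statistical analyses: "Between group differences in choice of surgery will be tested using the chi-square statistic". Read to its end, the sentence adds an alternative, so that choice of surgery is to be "tested using the chi-square statistic or, if statistical adjustment is required for covariates, multiple logistic regression analysis". The trigger for adjustment comes just before, after a comparison of the arms on sociodemographic and clinical characteristics: "If the groups are not comparable on one or more background variables, those variables will be employed routinely as covariates in subsequent analyses".

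**Questionnaire outcomes.** These are analysed by analysis of (co)variance at 6 and 12 months. On covariates: "Where appropriate, sociodemographic and clinical background variables, as well as baseline scores on the outcomes of interest, will be used as covariates". Methods/Design places the first questionnaire before randomisation. Under Choice of surgical procedure, however, the ovarian-cancer and hereditary-risk items are asked only at follow-up, and the Satisfaction with Decision Scale refers to the surgical choice.

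Hospital appears in none of these analyses.

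**The concern.** Stratified, blocked allocation balances the arms within each hospital. If hospitals differ in how often women have bilateral mastectomy, that variation no longer contributes to the difference between arms, but an unstratified chi-square still counts it in the variance. The test then rejects too rarely under the null and loses some power.

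The logistic alternative does not close the gap. It depends on finding background variables that are not comparable, and a factor balanced by design will rarely be found so. The rule therefore tends to leave out the one factor that the design points to.

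For the scales, the gain from adjusting for a baseline score comes from its correlation with the outcome, not from any imbalance. Making its use discretionary puts that precision at risk and leaves open whether each scale is analysed with or without its baseline.

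**Working it through.** **1. The plan's own figure.** Inputs from Sample size: "80% power to detect a difference of 18% versus 5% in the uptake of bilateral mastectomy, with the p-value set at 0.05", with 170 and 85 women. Two-sided testing is assumed, because sidedness is not stated. With control rate 0.05, RGCT rate 0.18, d = 0.13, k = 2 and pooled rate (0.05 + 2 × 0.18)/3 = 0.1367:

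- n(control) = [1.96 √(1.5 × 0.1367 × 0.8633) + 0.8416 √(0.05 × 0.95 + 0.18 × 0.82/2)]² / 0.13² = 73.9, so 74, or 222 in total.
- With continuity correction, n' = (n/4)[1 + √(1 + 2(k+1)/(k n d))]² = 85.1, so 86, or 258 in total. This is close to the stated 255.

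At 85 and 170, exact enumeration gives power of 87.4% for the uncorrected chi-square and 82.4% with Yates' correction. The pooled normal formula gives 85.9%.

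**2. Chi-square against the hospital-stratified test.** The documents give no between-hospital variation, so a range of SDs on the logit scale is assumed. Each setting uses 8,000 simulated trials with 255 women, 12 hospitals and blocks of 9 (6:3), and the marginal rates are held at 5% and 18%. The null sets both arms to 13.7%. Hospitals are either equal (21 or 22 women each) or unequal (60, 45, 36, 27, 22, 18, 14, 11, 9, 6, 4, 3). CMH is the Cochran-Mantel-Haenszel test; the chi-square is uncorrected.

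| Hospitals | SD | Power: chi-square | Power: CMH | Size: chi-square | Size: CMH |
|---|---|---|---|---|---|
| equal | 0 | 87.0% | 86.9% | 4.8% | 4.8% |
| equal | 0.5 | 87.9% | 88.3% | 4.7% | 5.0% |
| equal | 1.0 | 87.2% | 89.1% | 4.2% | 5.2% |
| equal | 1.5 | 86.7% | 90.7% | 3.4% | 5.3% |
| unequal | 0 | 87.8% | 87.6% | 5.2% | 5.1% |
| unequal | 0.5 | 87.4% | 87.4% | 4.6% | 5.0% |
| unequal | 1.0 | 86.0% | 87.6% | 3.9% | 4.9% |
| unequal | 1.5 | 85.3% | 88.3% | 3.4% | 4.6% |

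The simulation error of a size near 5% is √(0.05 × 0.95/8000) = 0.24 points, so differences of a few tenths should not be read as real. The gain in power is about 0 to 4 points with equal hospitals and 0 to 3 with unequal ones.

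**3. Scales with a baseline.** The standard error of a difference in SD units is √(1/85 + 1/170) = 0.1328. The difference detectable with 80% power is (1.96 + 0.8416) × 0.1328 = 0.372 SD unadjusted. Adjusting for a baseline with correlation r multiplies this by √(1 − r²), and the effective sample size is 255/(1 − r²). The documents do not give r.

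| r (assumed) | Detectable difference | Effective N |
|---|---|---|
| no adjustment | 0.372 SD | 255 |
| 0.3 | 0.355 SD | 280 |
| 0.5 | 0.322 SD | 340 |
| 0.7 | 0.266 SD | 500 |

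At the planned 0.5 SD, power is 96.4% unadjusted and 99.1% at r = 0.5.

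**4. Events.** Expected bilateral mastectomies: 85 × 0.05 + 170 × 0.18 = 4.25 + 30.6, about 35 over 12 hospitals. Eleven hospital indicators in an ordinary logistic model could be unstable with so few, which favours CMH.

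**The case against.** The best defence is that little is lost. An unstratified chi-square after stratified randomisation errs on the safe side, and its power already exceeds the plan. With an SD of 0 or 0.5, stratifying changes almost nothing. The larger SDs are wide: around 5% uptake, an SD of 1.0 implies hospitals from about 0.7% to 27%, and 1.5 from about 0.3% to 50%. The scales are comfortably powered for 0.5 SD, and analysis of covariance with baseline scores is already named. Its conditional wording may simply mean that a baseline is used where one exists. All this stands and limits the size of the point.

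It could also be said that such choices belong in an analysis plan that is not shown. That stands only in part: the article states the default test, the trigger for adjustment and the conditional use of baseline scores, so the point concerns a stated method.

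A reader might infer more than the text supports:

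- *The surgery test is always an unadjusted chi-square.* Logistic regression is allowed, though on a trigger unlikely to bring in hospital.
- *Every key scale has a baseline.* Some risk items are asked only at follow-up, and a pre-randomisation score for satisfaction with the surgical decision is doubtful.
- *Separate 6- and 12-month models lose the 17% expected to drop out.* Separate models are a natural reading but are not stated. The 17% is overall attrition, from 306 to 255. It does not count women who miss one questionnaire and return the other, so it does not measure what a mixed model would recover.
- *The trial is underpowered or at risk of false positives.* Neither follows; the error is towards conservatism.

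**Conclusion.** The point holds as a modest, inexpensive improvement. The stated analyses ignore the randomisation stratum and do not commit to using baseline scores.

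For surgery, the chi-square's size falls from about 5% to about 3.4% as the assumed hospital SD rises from 0 to 1.5, with 0 to 4 points of power lost. The required sample size does not change, and simulated chi-square power stays at 85% or more in every setting. That rests on assumed hospital sizes and variation, two-sided testing and no continuity correction. With Yates' correction, power is 82.4% before any hospital variation; the simulation did not cover that version with variation.

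For the scales, the possible gain is larger but depends on the assumed correlation and applies only to scales with a baseline. It sharpens estimates and does not rescue power for the planned 0.5 SD.

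**What to change.** - **Surgery.** Make the primary test a Cochran-Mantel-Haenszel test stratified by hospital, reported with a Mantel-Haenszel risk difference and 95% CI. Fix the rule for pooling small hospitals in advance. Apply the test whatever the observed baseline balance, so that the primary method no longer depends on the comparison of the arms at entry.
- **Scales.** For each questionnaire scale with a pre-randomisation score, always include that score and hospital as covariates. List these scales, leaving out items asked only at follow-up and scales about the later surgical decision.
- **Optional.** A mixed model over 6 and 12 months would use every woman with at least one follow-up questionnaire, but the point does not depend on it.

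The cost is a change of wording and a few lines of code. The downside is that very small hospitals contribute little to the stratified test, hence the pooling rule.

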The number of contacts between the patient and the clinical geneticist prior to surgery depends on the complexity of each individual case. For women who choose not to undergo DNA testing, this may be limited to a single session. For women who undergo DNA testing, at least one additional session is held in order to discuss the DNA test results. All results of the RGCT are forwarded to the treating surgeon, and consultation between the clinical geneticist and surgeon takes place prior to and following the patient's first appointment with the clinical geneticist.

Psychosocial support is offered routinely to all women who opt for rapid DNA testing, *BRCA1/2 *carriers and to all women who are considering undergoing BLM regardless of whether they have undergone DNA testing. Where appropriate, referrals are made to mental health caregivers in the hospital. The need for and uptake of more intensive psychosocial care during subsequent treatment are being assessed as part of the study.

Women in the UC condition receive standard advice and care from their treating surgeon. In relation to the possible hereditary nature of their disease, this typically involves discussion of the family history and of appropriate surgical options. In some cases, patients may be referred for genetic counseling or may self-refer. However, in current practice, this occurs rarely during the pre-surgery period [38,39].

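### With 2:1 allocation, the psychosocial ANCOVA should use standard errors that allow the arms to differ in spread (a low-cost improvement, not a demonstrated error)

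*Protocol article*

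**What the plan says.** The Statistical analyses section of the protocol article names the method for risk perception, distress, knowledge, decisional satisfaction and quality of life: "Analysis of (co)variance will be employed to assess group differences at 6 and 12 month follow-up". It adds that background variables, "as well as baseline scores on the outcomes of interest, will be used as covariates" where appropriate. It gives no variance estimator and does not mention unequal variances.

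The Sample size section fixes unequal arms, "170 in the RGCT arm and 85 in the UC arm", and explains that "The sample size ratio of 2:1 was chosen to ensure that the RGCT sample is sufficiently large" for estimates among carriers. It states the detectable psychosocial difference as half a standard deviation, with one SD for both arms. No SD by arm is given for any scale.

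Two statements bear on spread:

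- Sample size expects 20% of the RGCT arm to test positive.
- Intervention says of usual-care (UC) women: "In some cases, patients may be referred for genetic counseling or may self-refer". It calls this rare only before surgery. The Abstract and the Discussion describe counselling and testing after primary treatment as common practice, and the Abstract gives 4 to 6 months for results.

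**The concern.** Ordinary ANOVA or ANCOVA estimates one residual variance for both arms. With equal arms, unequal spread hardly disturbs the standard error of the difference. With 170 against 85, the pooled variance is dominated by the larger arm, while the true variance of the difference is dominated by the smaller one. If RGCT scores are more spread out, the pooled standard error is too wide. If UC scores are more spread out, it is too narrow.

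Both directions have a plausible source here. Telling about a fifth of the RGCT arm that they carry a mutation could widen perceived risk and worry in that arm. Counselling that reaches only some UC women by follow-up could widen genetic knowledge in the smaller arm, because the Background reports that most studies find counselling raises knowledge. Hypotheses 3 to 5 rest on these comparisons, and the direction of bias could differ between outcomes, so one general caveat would not cover them all.

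**Working it through.** **The plan's own figures.** The expected RGCT uptake reproduces: 0.2 × 0.5 + 0.8 × 0.1 = 18%. For 18% versus 5% at two-sided 0.05 and 2:1, the continuity-corrected formula gives 86 + 172 = 258, close to 255; power at 85/170 is 79.9%. For a 0.5 SD difference with equal spread, power at 85/170 is 96.4%, which agrees with the article's view that the sample is ample for these outcomes.

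**Inputs from the article.** n1 = 170 (RGCT), n2 = 85 (UC), 20% carriers.

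**Assumed inputs.** A shift of D = 1 to 2 within-group SD between subgroups; the share of UC women counselled or tested by follow-up (one half); RGCT uptake (80%, 90% or 100%).

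**Formulas.** If a share p of an arm is shifted by D, its variance is v = 1 + p(1 − p)D², in within-group units. Then

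- pooled SE = sqrt{[(169·v1 + 84·v2)/253] × (1/170 + 1/85)}
- true SE = sqrt(v1/170 + v2/85)
- q = pooled SE / true SE
- type I error = 2[1 − Φ(1.96q)]; interval coverage = 1 minus this.

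With v1 = v2, q = 1 and the type I error is 5%.

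**Risk perception and worry.** With p = 0.2 in RGCT, v1 = 1 + 0.16D². If no UC woman knows her status, v2 = 1. If half of UC is tested with the same 20% positive, p = 0.1 and v2 = 1 + 0.09D².

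| UC women | D | v1 | v2 | q | Type I error |
|---|---|---|---|---|---|
| none tested | 1 | 1.16 | 1.00 | 0.1398/0.1363 = 1.025 | 4.45% |
| none tested | 2 | 1.64 | 1.00 | 0.1587/0.1463 = 1.085 | 3.35% |
| half tested | 1 | 1.16 | 1.09 | 0.1416/0.1402 = 1.010 | 4.8% |
| half tested | 2 | 1.64 | 1.36 | 0.1652/0.1602 = 1.032 | 4.3% |

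**Genetic knowledge.** With half of UC counselled, v2 = 1 + 0.25D². With RGCT uptake u, v1 = 1 + u(1 − u)D².

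| RGCT uptake | D | v1 | v2 | q | Coverage |
|---|---|---|---|---|---|
| 80% | 1 | 1.16 | 1.25 | 0.988 | 94.7% |
| 90% | 1 | 1.09 | 1.25 | 0.977 | 94.5% |
| 80% | 2 | 1.64 | 2.00 | 0.967 | 94.2% |
| 90% | 2 | 1.36 | 2.00 | 0.938 | 93.4% |
| 100% | 1 | 1.00 | 1.25 | 0.964 | 94.1% |
| 100% | 2 | 1.00 | 2.00 | 0.894 | 92.0% |

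**Smaller shifts.** At D = 0.5 the standard error is 0.7% too wide for risk (none of UC tested) and 1.0% too narrow for knowledge (full uptake, half of UC counselled). Both are negligible.

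**Outcomes driven by surgery (hypothesis 5).** With bilateral mastectomy in 18% versus 5% and D = 1, v1 = 1 + 0.18 × 0.82 = 1.148 and v2 = 1 + 0.05 × 0.95 = 1.048, so q = 1.015.

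**Does the remedy work?** An ANCOVA was simulated with 170/85 women, baseline correlation 0.5 and 4,000 runs per setting (Monte Carlo error about 0.3 points at 5%).

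| SD ratio RGCT/UC | Pooled SE | HC3 |
|---|---|---|
| 0.67 | 8.6% | 4.8% |
| 0.80 | 6.8% | 4.9% |
| 1.00 | 5.4% | 5.3% |
| 1.25 | 3.7% | 5.0% |
| 1.50 | 2.6% | 5.3% |

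HC3 stays near 5% throughout and costs nothing visible when spreads are equal.

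**The case against.** The strongest reply is that the article names a model family and nothing more. It never says the variances are assumed equal, and a journal article commonly leaves the variance estimator to the full protocol or analysis plan, which is not shown. ANCOVA with robust errors would still be the analysis the article names. This stands: nothing in the article is false or contradictory on this point, and if the full plan already specifies robust errors, nothing need change.

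Three stronger readings are tempting, and the documents do not support them.

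- **That the planned standard errors are wrong.** No SD by arm is given, and hypotheses 3 to 5 concern levels, not spread. Bias is conditional on a difference in spread that the design only makes plausible. The two extreme cases also cannot be combined freely. If half of UC women are counselled and tested by follow-up, which the knowledge case needs for counselling, the risk case shrinks to 1% to 3% too wide. The knowledge case shrinks in turn because Intervention allows women to decline RGCT and the intention-to-treat rule keeps them in the arm.
- **That hypothesis 4 would produce false positives above 5%.** For knowledge, the extra spread arises only because counselling raises knowledge and reaches different shares of the arms. With all of RGCT and half of UC counselled, the true difference is 0.5D, that is 0.5 to 1.0 within-group SD. The null is then false, so what suffers is interval coverage. For decisional satisfaction, also part of hypothesis 4, no source of unequal spread has been identified.
- **That hypothesis 3 loses material power.** For a difference of 0.5 within-group SD with no UC woman tested, power with the pooled versus the correct standard error is 95.1% versus 95.6% at D = 1, and 90.2% versus 92.7% at D = 2.

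What survives is that the analysis is named, the 2:1 ratio is fixed, and the default form is sensitive to unequal spread in a design that gives some reason to expect it.

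**Conclusion.** The point holds as a low-severity, free improvement. For risk perception and worry the pooled standard error would be about 1% to 8% too wide, with type I error of about 4.8% to 3.4% (nearer 4.8% to 4.3% if half of UC women are also tested). For knowledge, with half of UC counselled, it would be about 1% to 6% too narrow at 80% to 90% RGCT uptake, with coverage of about 94.7% to 93.4%. The figure of 11% too narrow, with coverage of about 92%, needs full uptake and a 2 SD counselling effect.

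All these sizes rest on assumed shifts, UC shares and uptake; only the arm sizes and the 20% carrier share come from the article. The primary surgical outcome is analysed by chi-square or logistic regression and is unaffected.

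**What to change.** Keep the ANCOVA and add one sentence to the Statistical analyses text, or to the analysis plan if it does not already say so: all between-arm comparisons of psychosocial outcomes at 6 and 12 months use heteroscedasticity-consistent (HC3) standard errors, or a model with arm-specific residual variances. Fixing this in advance also avoids choosing the estimator after seeing the follow-up data.

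The cost is one sentence and one software option. It needs no extra patients or data, and the loss is negligible if the spreads turn out equal.
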